### Sample size

This study will be designed to detect a difference of *d* = 0.40 between the groups as the primary outcome. As patients expect to be treated for their depression in the subsequent inpatient psychotherapeutic treatment, we do expect a somewhat smaller effect size for our intervention than what has been found in the most recent meta-analysis of internet-based guided self-help treatments for depression [35]. With a power of 0.80 in a two-tailed test and *α* = .05, a sample of *n* = 200 participants would need to be included at baseline (calculated using GPower 3.1).

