### Statistical analyses

This clinical trial will be conducted in compliance with the protocol of the Declaration of Helsinki and GCP. Aiming at an intention-to-treat design we will include all participants who will be randomly assigned to conditions. Additional per protocol analyses (PPA) will be conducted, including only participants’ satisfying protocol treatment.

Missing data will be handled using multiple imputations (MI). MI is especially robust with respect to missing data [69]. Nevertheless, to assess systematic effects of missing data that cannot be ignored, pattern mixture analyses for multi-level longitudinal approaches [70] will be conducted. To determine whether the treatment effect is dependent on missing data, the missing-data pattern of each participant will first be coded and then included in a three-way interaction (missing-data pattern x condition x change in depression severity) in the main outcome analyses. If no significant interactions between the missing-data pattern and the treatment outcome are found, it can be concluded that it is very unlikely that missing data skewed the results.

The mean improvement scores on all continuous outcome measures will be analysed within and between groups via mixed-model analyses of variance. For all mixed-model analyses, Cohen’s *d*[71] will be calculated by standardising the differences between baseline and follow-up scores by the pooled standard deviation of baseline scores.

The clinically significant improvements between pre-treatment and post-treatment will be examined with regard to the definition of Kroenke (2002) [58]. Differences in response and remission rates will be analysed using chi-square tests. We will also calculate the number needed to be treated (NNT) to achieve response, partial remission, or remission. Time to remission will be measured in days, and the differences between groups in time to remission will be compared using a t-test for independent samples.

Analyses will be performed using an alpha level of 0.05 and one-sided tests will be used for unidirectional and two-sided tests for bidirectional hypotheses. All analyses will be conducted using SPSS 21.

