## Discussion

Major depression is a prevalent and severe disorder. Several circumstances lead to the fact that patients remain untreated despite their urgent need for help. Web-based treatments may be an appropriate way of bridging the time gap for patients on a waiting list. Using waiting time efficiently by introducing patients to upcoming therapeutic components before the start of inpatient therapy might be a promising approach to reduce the burden of disease for the patients, to promote earlier discharges and, as a result, to achieve shorter waiting times for subsequent patients.

This study will probably contribute to the literature by evaluating a new web-based intervention for depression compared to treatment as usual in patients on a waiting list for inpatient psychotherapy in a rater-blind randomised controlled trial. We will (a) test the main hypothesis that providing patients access to internet-based, guided self-help will lead to reduced symptom severity before inpatient treatment starts. Moreover, we will (b) investigate whether patients achieve remission earlier and (c) whether we can find significantly more patients with remission or response at the end of inpatient treatment.

There are several strengths to this study: This study will likely be one of the first randomised controlled studies that investigates a web-based intervention for patients on a waiting list for inpatient psychotherapy. We will also (a) use validated clinician-rated measures administered by independent raters blind to treatment condition in addition to self-report, (b) include a specific sample defined by standard diagnostic measures, (c) implement an appropriate statistical analysis plan, and (d) use state-of-the-art methods to cope with missing data.

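### The sidedness of the primary test is stated inconsistently: the trial is sized on a two-tailed test at 0.05, while the analysis rule, read literally, makes the test one-sided at 0.05

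*Protocol article*

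**What the plan says.** Three parts of the protocol article bear on this point.

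- **Sample size.** The target effect is d = 0.40. The basis for 200 patients is given as "With a power of 0.80 in a two-tailed test and *α* = .05". This is the only place where a sidedness is attached to the primary outcome.
- **Statistical analyses.** The general rule reads "Analyses will be performed using an alpha level of 0.05", and the same sentence continues that "one-sided tests will be used for unidirectional and two-sided tests for bidirectional hypotheses". Alpha is not reduced for one-sided tests, the primary outcome is not set apart, and no hypothesis is labelled as one kind or the other.
- **Discussion, and Trial objectives and purpose.** The Discussion says that the trial will "test the main hypothesis that providing patients access to internet-based, guided self-help will lead to reduced symptom severity before inpatient treatment starts". The objectives likewise ask whether the intervention lowers depressive severity relative to usual treatment. Both name a single direction.

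**The concern.** Sidedness is part of the rule for declaring the intervention effective. Here it depends on how a hypothesis is labelled, and the protocol does no labelling. An analyst who follows the Sample size section tests two-sided at 0.05. An analyst who takes the directional wording of the main hypothesis and applies the analysis rule tests one-sided at 0.05. Either could cite the published text, and nothing stops the choice being made after the result is known.

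The two readings disagree for favourable results with a two-sided p between 0.05 and 0.10: the first calls such a trial inconclusive, the second positive. The one-sided reading also leaves no formal means of concluding that the intervention arm did worse than usual treatment.

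**Working it through.** **Inputs.** From the Sample size section: d = 0.40, power 0.80, two-tailed alpha 0.05, total N = 200. From the Statistical analyses section: alpha 0.05 for all analyses, one-sided where the hypothesis is unidirectional. Assumptions, because the article does not state them: 1:1 allocation (100 per arm), a two-sample t-test, and all 200 patients analysed.

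**Step 1: reproduce the stated sample size.** By the normal approximation, n per arm = 2(z_alpha + z_power)² / d².

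- Two-sided 0.05: 2(1.960 + 0.842)² / 0.16 = 98.1, so 99 per arm, 198 in total.
- One-sided 0.05: 2(1.645 + 0.842)² / 0.16 = 77.3, so 78 per arm, 156 in total.

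With the exact noncentral t distribution, the two-sided design needs 100 per arm (200) and the one-sided design 78 per arm (156). The stated 200 is correct, and it fits the two-sided design only.

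**Step 2: compare the two readings at 100 per arm.** The noncentrality at d = 0.40 is 0.40 × √(100/2) = 2.828, with 198 degrees of freedom. The smallest observed d that reaches significance is the critical t times √(2/100) = 0.1414.

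| | Two-sided 0.05 (Sample size section) | One-sided 0.05 (analysis rule, literal) |
|---|---|---|
| Chance of a false claim of benefit | 0.025 | 0.05 |
| Critical t | 1.972 | 1.653 |
| Smallest significant observed d | 1.972 × 0.1414 = 0.279 | 1.653 × 0.1414 = 0.234 |
| Power at d = 0.40 | 0.804 | 0.880 |
| N for 80% power | 200 | 156 |

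**Step 3: the zone where the readings disagree.** It runs from an observed d of about 0.23 to about 0.28 in favour of the intervention. With no true effect, a trial lands there with probability 0.05 − 0.025 = 0.025. With a true d of 0.40, the probability is about 0.880 − 0.804 = 0.076.

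**Step 4: the named primary analysis.** The plan names a mixed-model analysis of variance. HRSD-24 is measured at two time points (Table 1) in two groups, so the group-by-time F test has one numerator degree of freedom and equals t². Its printed p-value is two-sided. A one-sided reading would mean halving that p-value when the effect is favourable, a step that the article neither describes nor excludes.

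**Step 5: check of the remedy.** A one-sided test at 0.025 with 100 per arm also has power 0.804. It therefore matches the two-tailed 0.05 design for a claim of benefit.

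**The case against.** The strongest reply is that the specific statement governs the general one. Only the Sample size section ties a sidedness to the primary outcome, and it says two-tailed. The analysis rule is generic. The directional wording stands in the Discussion and in the statement of aims, not in a Methods description of the test. On that reading the primary test is two-sided and nothing is inflated. This is a fair reading, and it is why the doubled error must be stated as conditional. A reader might infer that the primary test will run at twice the planned rate. The document does not support that, because it never classifies the main hypothesis as unidirectional. The reply does not remove the conflict, though: a hypothesis that predicts a reduction is unidirectional in ordinary usage, and the analysis rule makes no exception for it.

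A reader might also infer that the rule cannot apply to the named tests, on the ground that F and chi-square tests have no one-sided form. That is wrong here. The two-group, two-time-point F and the 2×2 chi-square each have one degree of freedom and a directional version through the signed square root. The independent-samples t-test planned for time to remission has an ordinary one-sided form. If the inference were right, it would also rule out the doubling.

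Three further points stand. Nominal alpha is 0.05 on either reading; only the error in the direction of benefit changes, and 2.5% is implied by the two-tailed design, not stated. The questions about remission during inpatient therapy are described as exploratory, so they add little to a concern about confirmatory error. The power figures are for a two-sample t-test, not for the pre/post mixed model.

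**Conclusion.** The inconsistency is real and concerns the success criterion for the primary outcome. The sample size rests on a two-tailed test at 0.05. The analysis rule, applied literally to a main hypothesis worded as a reduction, gives a one-sided test at 0.05. On that literal reading the chance of a false claim of benefit is 5% instead of 2.5%, and the threshold on observed d drops from about 0.28 to about 0.23. On the other available reading there is no inflation. The article does not say which reading applies.

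The sample-size arithmetic is sound, and neither reading leaves the trial short of power at d = 0.40. The thresholds and power figures rest on the assumptions listed in the working; the 5% against 2.5% comparison does not depend on the allocation ratio. The point should be settled before analysis, because it decides what counts as a positive trial.

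**What to change.** Amend the sidedness sentence in Statistical analyses to state that the between-group comparison of HRSD-24 is tested two-sided at alpha 0.05 (equivalently, one-sided at 0.025 for a claim of benefit), in agreement with the Sample size section. Preferably apply the same to the other between-group tests, although the contradiction itself requires this only for the primary comparison. If one-sided tests are kept for any secondary or exploratory question, list those hypotheses and their direction in advance.

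The cost is one sentence. N = 200 and the planned power of 0.80 are unchanged. All that is given up is the extra power (0.880 against 0.804) that a one-sided 0.05 test would have had, which the sample-size calculation never relied on.

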## Discussion

Major depression is a prevalent and severe disorder. Several circumstances lead to the fact that patients remain untreated despite their urgent need for help. Web-based treatments may be an appropriate way of bridging the time gap for patients on a waiting list. Using waiting time efficiently by introducing patients to upcoming therapeutic components before the start of inpatient therapy might be a promising approach to reduce the burden of disease for the patients, to promote earlier discharges and, as a result, to achieve shorter waiting times for subsequent patients.

This study will probably contribute to the literature by evaluating a new web-based intervention for depression compared to treatment as usual in patients on a waiting list for inpatient psychotherapy in a rater-blind randomised controlled trial. We will (a) test the main hypothesis that providing patients access to internet-based, guided self-help will lead to reduced symptom severity before inpatient treatment starts. Moreover, we will (b) investigate whether patients achieve remission earlier and (c) whether we can find significantly more patients with remission or response at the end of inpatient treatment.

There are several strengths to this study: This study will likely be one of the first randomised controlled studies that investigates a web-based intervention for patients on a waiting list for inpatient psychotherapy. We will also (a) use validated clinician-rated measures administered by independent raters blind to treatment condition in addition to self-report, (b) include a specific sample defined by standard diagnostic measures, (c) implement an appropriate statistical analysis plan, and (d) use state-of-the-art methods to cope with missing data.

This trial has also several limitations: As the trial will be conducted within the context of routine mental health care, the time span between the post-treatment assessment (conducted after the web-based treatment) and the beginning of inpatient therapy depends on both the capacities of the clinic and the eagerness of the patient and therefore will vary between patients. We will assess post-treatment data in both conditions at three weeks after randomisation to ensure a comparable time frame. Hence, patients will be at varying states within the online training when the post-treatment assessment takes place. Furthermore, we chose not to include a placebo/attention control condition because the TAU condition cannot be foreknown and is expected to be quite heterogeneous. Besides it is our aim is to study the effectiveness of GET.ON Mood Enhancer-WL in addition to and compared with usual care, as is standard in pragmatic trials [72]. However, due to the lack of such an active control condition, the mechanisms responsible for any possible effects will remain unclear. Last, we will include follow-up assessments only until the end of inpatient treatment. Therefore, we cannot draw conclusions about the effects on the long-term course of symptoms.

In the long term, it would be a desirable step to increasingly implement a new procedure such as this into the daily routine of inpatient as well as outpatient therapy. It would be good practice for the therapist to know in detail what steps the patient has taken previously and to be able to continue the previous gains. This knowledge would assist both the patient and the therapist, saving time and effort, and allowing them to concentrate on further issues and to intensify the treatment process.

Future research could make use of a homogenous control group, focus on various modifications of the program to identify active ingredients, compare different interventions that are likely to be effective as pre-inpatient treatments, evaluate web-based interventions for other disorders than depression or change the setting into the field of outpatient therapy.
